## Abstract

**Background:**

Insight regarding transfusion practices in Hematopoietic Stem cell Transplantation (HSCT) are lacking and the impact of red cell transfusion in this high risk group on outcomes following HSCT are not well appreciated. Red blood cell transfusion can be life-saving, however, liberal use of transfusion in critically ill patients failed to demonstrate significant clinical benefit. A large number of other observational studies have also demonstrated an association between red blood cell transfusions and increased morbidity such as infections and multi organ failure as well as increased mortality. The role of red cell transfusion on the clinical outcomes observed in patients undergoing HSCT remains poorly understood and a prospective randomized study of transfusion is required to gain insight and knowledge on best transfusion practices in this high risk population.

**Methods:**

This report describes the design and methodological issues of a randomized pilot study evaluating red cell transfusion triggers in the setting of Hematopoietic Stem Cell Transplantation. This study has been funded by a peer review grant from the Canadian Blood Services and is registered on Clinicaltrials.gov NCT01237639.

**Results:**

In 3 Canadian centres, 100 patients undergoing Hematopoietic Stem Cell Transplantation will be randomized to either a restrictive (target hemoglobin of 70-90 g/L) or liberal (target hemoglobin of 90-110 g/L) red cell transfusion strategy, based daily hemoglobin values up to 100 days post-transplant. The study will stratify participants by centre and type of transplant. The primary goal is to demonstrate study feasibility and we will collect clinical outcomes on 1) Transfusion Requirements, 2) Transplant Related Mortality, 3) Maximum grade of acute Graft versus Host Disease, 4) Veno-occlusive Disease, 5) Serious Infections, 6) Bearman Toxicity Score, 7) Bleeding, 8) Quality of Life, 9) Number of Hospitalizations and 10) Number of Intensive Care Unit (ICU) Admissions.

**Conclusion:**

Upon completion, this pilot trial will provide preliminary insight into red cell transfusion practice and its influence in hematopoietic stem cell transplant outcomes. The results of this trial will inform the conduct of a larger study.

## 1. Background

Evidence based transfusion practices in Hematopoietic Stem cell Transplantation (HSCT) are lacking and the impact of red cell transfusion on outcomes following HSCT are not well appreciated. Although, red blood cell transfusion can be life-saving, liberal use of transfusion in critically ill patients failed to demonstrate significant clinical benefit in a landmark Canadian study [1]. In fact, increased 30 day mortality was observed in a subset of patients transfused at a higher hemoglobin level and red blood cell transfusion may contribute to impaired wound healing in various other settings. In one single-centered retrospective study, patients undergoing allogeneic transplantation who had reduced hemoglobin at the time of transplant received a greater number of red cell transfusions and had increased transplant-related mortality [2]. Similar results were obtained in a multi-centered study coordinated by one of the authors [3] and reduced hemoglobin prior to autologous transplantation is associated with greater number of transfused red cell units and increased toxicity [4]. Moreover, a recent study suggests that red cell transfusion in cancer patients is associated with increased risk of thrombosis and in-hospital mortality [5]. Our systematic search of the literature on transfusion strategies in HSCT reveals a paucity of knowledge, in particular an absence of definitive clinical studies.

The most compelling evidence that red cell transfusion may be harmful is derived from the TRICC study [1]. In 838 critically ill patients randomized to a restrictive transfusion strategy (target hemoglobin of 70-90 g/L with a hemoglobin transfusion threshold of 70 g/L), or a liberal transfusion strategy (target hemoglobin of 100-120 g/L with a hemoglobin transfusion threshold of 100 g/L), patients in the restrictive arm had lower hemoglobin levels (received fewer red cell transfusions, and had lower mortality at 30 days). The results from this seminal trial demonstrated that a restrictive red blood cell transfusion strategy reduces red cell transfusion requirements and is at least as safe as, and possibly superior to, a more liberal approach for critically ill adults. These data showing that restrictive transfusion triggers can reduce red cell transfusion use without significantly increasing adverse clinical outcomes have been replicated in pediatric [6] and neonatal ICU [7] patients. Additionally, in a recent systematic review of 45 observational trials, red cell transfusions were associated with an increased risk of infection, multi-organ failure, and death [8].

With regards to the HSCT population, Xenocostas et al [2] reported that patients undergoing allogeneic transplantation required an average of 6.8 ± 6.4 units of red cells between 0 - 60 days after transplant and the frequency of red cell transfusion decreased significantly thereafter. Increased numbers of red cell transfusions were associated with the before-transplant hemoglobin level, major ABO mismatch between donor and recipient, transplantation in patients with more advanced disease, with the use of unrelated compared with related donors, older patient age and female gender. The before transplant hemoglobin level was also associated with increased mortality within 6 months of transplant in multivariate regression analysis. The association of reduced hemoglobin prior to allogeneic HSCT with increased red cell transfusion requirements and increased 180-day mortality was confirmed in a multi-centered analysis [3]. With regards to patients undergoing autologous transplantation, reduced hemoglobin prior to HSCT was associated with increased red cell transfusion requirements in a study recently published by our group. Furthermore, reduced hemoglobin on the day of stem cell collection was associated with lower levels of vascular progenitor cells in the stem cell collection and increased organ-specific toxicity following high-dose chemotherapy [4].

Conceptually, higher hemoglobin levels would correlate with better performance status and/or quality of life. Indeed, there have been positive associations noted between a higher hemoglobin and quality of life in a variety of clinical populations [9-13]. Nonetheless, there is a paucity of data in the transplant literature reviewing the impact of hemoglobin levels and quality of life. However, a reduced hemoglobin level prior to transplantation has been associated with increased post transplant mortality and toxicity [2]. It remains unclear whether improvements in hemoglobin levels prior and/or during transplant would abrogate these negative outcomes. The role of red cell transfusion on the clinical outcomes observed in patients undergoing HSCT remains poorly understood and a prospective randomized study of transfusion is required to gain insight and knowledge on best transfusion practices in this high risk population.

In preparation for our trial, all adult transplant centres associated with the Canadian Blood and Marrow Transplant Group (n = 15) were asked to respond to a survey regarding transfusion thresholds for red cells. Fourteen centres routinely transfuse 2 units of Packed Red Blood Cells (PRBC) when the hemoglobin < 80 g/L and/or in response to patient specific indications. One centre transfuses PRBCs when the hemoglobin < 70 g/L and/or response to specific circumstances. Importantly, the rationale for the near universal adoption of red cell transfusion trigger of 80 g/L (personal communication with Canadian transplant Directors) remains unclear. There appears to be a reluctance to fully embrace a hemoglobin trigger of 70 g/L as suggested by the TRICC study, recognizing that there are differences between ICU and HSCT patients. This may have lead to a "middle of the road" approach, with centres selecting a trigger of 80 g/L with historical red cell transfusion triggers as high as 100 g/L.

Our coordinating centre has historically adopted a red cell transfusion trigger of 80 g/L and we recently conducted an audit of our transfusion practices for the year 2009. Despite our established trigger of 80 g/L, red cell transfusions above this trigger occurred in 50% of all transplant patients ever requiring red cells within the 1^st ^100 days of the transplant. Further, 20% of all red cell transfusion episodes occurred above the stated trigger. This phenomenon has also been observed in other Canadian centres (personal communication).

No centre has clearly embraced a liberal transfusion strategy and only 1 centre has embarked on a more restrictive strategy. This indicates some relative uncertainty with regards to the benefits and harms of PRBC transfusion in the HSCT population. If we assume that the current threshold may be associated with some potential for harm and some potential for benefit, it is reasonable to consider whether transfusion at 70 g/L is better or worse than transfusing at 90 g/L.

This report describes our design and methods of TRIST, an open labeled multi-center pilot randomized controlled trial in adult patients undergoing HSCT to assess if restrictive strategy to maintain a hemoglobin greater than 70 g/L compared to a more liberal strategy of maintaining hemoglobin greater than 90 g/L is safe and associated with reduced transplant-related mortality following HSCT. This trial will focus on feasibility outcomes in order to facilitate the planning and conduct of a definitive phase III trial.

## 2. Methods

### 2.1 Trial Overview

TRIST is an open-labeled multi-center pilot parallel-arm randomized controlled trial, where participants will be stratified by centre (3 centres) and type of HSCT (either autologous or allogeneic). We will recruit patients over a 2 year period and follow each participant for a minimum of 100 days. Following a screening visit to confirm eligibility, patients will be randomized with subsequent study assessments to occur in concert with routine transplant care on Days +7, +14, +28, +60, +100 (where Day 0 is defined as the 1 ^st ^day of stem cell infusion). TRIST has been funded by a peer reviewed grant by the Canadian Blood Services (R & D Intramural Grants Competition 2010) and registered on the National Institute of Health, Clinicaltrials.gov registry (NCT01237639).

### 2.2 Study participants

Study participants will be recruited from 3 Canadian adult HSCT centers. They will be adult recipients of either an autologous or allogeneic HSCT. We chose to study both populations to 1) better appreciate the potential benefits and/or harms with our intervention in these 2 different types of HSCT and 2) to help define a feasible primary endpoint for a definitive clinical trial. Specific inclusion and exclusion criteria are listed in Table 1.

**Table 1 T1:** Inclusion and Exclusion Criteria

	*Inclusion Criteria*
1	Males or females aged 18 years or older who are undergoing either an autologous or allogeneic HSCT.

2	The indications for HSCT may include, but not limited to the following diseases: a. Acute Leukemia, myeloid, lymphoid or biphenotypic in 1^st^, 2^nd ^remission or in relapse b. Chronic Myeloid Leukemia in chronic, accelerated or blast phase c. Chronic Lymphocytic Leukemia d. Myelodysplastic Syndrome e. Myeloproliferative Disorder f. Lymphoma g. Myeloma

3	All study patients must provide consent at least 1 day prior to scheduled HSCT and provide written informed consent.

	***Exclusion Criteria***

1	Pregnant or lactating at the time of enrollment.

2	Already received red cell transfusion after conditioning chemotherapy for HSCT but prior to enrollment.

3	Unable/unwilling to providing informed consent.

4	Geographically inaccessible

### 2.3 Allocated treatment strategies

Eligible participants will have daily (morning) laboratory investigations, including a Complete Blood Count (CBC) performed as standard of care. The recipient will be randomized to one of two red cell transfusion strategies, to be carried out based on daily morning CBCs (The transfusion strategy will be carried out from Day 0 until Day 100 post stem cell infusion/transplant):

1. Liberal Strategy (Red cell transfusion trigger of 90 g/L): Participants will receive 2 units of packed red blood cells if the Hemoglobin (Hb) level is < 90 g/L, based the day's CBC to target a Hb level of 90-110 g/L

2. Restrictive Red cell Transfusion Strategy (Red cell transfusion trigger of 70 g/L): Participants will receive 2 units of packed red blood cells if the Hb level is < 70 g/L, based on the day's CBC to target a Hb level of 70-90 g/L

Transfusion(s) of red cells outside the red cell transfusion strategy is permitted when clinically indicated by the treating physician.

### 2.4 Randomization and treatment allocation

The randomization process will consist of a computer generated random list of permutated blocks of 2 and 4, stratified by type of HSCT (autologous or allogeneic) and by centre (3 centres). The randomization sequence will be determined by the Ottawa Hospital Research Institute-Methods Centre statistician, independent from the study. After screening the patient for eligibility and obtaining informed consent, the study nurse will randomize the patient using the number in the next chronological order from the randomization lists provided ahead of time by the Methods Centre. This randomization list is secured within a password protected SQL server. The participant's assignment is only known once all the inclusion criteria are reviewed and "checked-off" online. The local research coordinator/nurse will then identify the transfusion intervention assignment of the participant to the HSCT team.

### 2.5 Medical Management

In addition to the primary intervention of assignment of either a restrictive or liberal transfusion strategy, all other HSCT support care will be according to local institutional practice. This will include, but not limited to the use of antibiotics, analgesia, intravenous fluids, growth factors and blood products (not including red cells).

### 2.6 Withdrawal from study

Participants may withdraw from the study at any time and for any reason, or maybe withdrawn at the treating physician's discretion in the event of intolerance to transfusion assignment, adverse events, or administrative reasons.

### 2.7 Study Outcome measures: Feasibility

The primary goal of this pilot study is to demonstrate feasibility. We will (1) identify logistical issues related to protocol implementation. Further, we will evaluate feasibility of (2) recruitment rates, (3) randomization implementation strategy, (4) data collection of clinical outcomes and (5) define the sample size required for a definitive trial. To evaluate the feasibility of recruitment, we will seek to demonstrate the ability to recruit 3 patients per centre per month (based on investigator consensus).

We also seek to document compliance with the assigned red cell transfusion threshold. Compliance will be assessed by the number of protocol violations for red cell transfusions (participants receiving PRBCs above or below the assigned transfusion trigger in the absence of a clinical rationale e.g. angina). We have arbitrarily defined compliance (based on total PRBC transfusion episodes) to the assigned red cell transfusion threshold as follows: Excellent (≤5% violations), Acceptable (between 5% and 20% violations), Poor (≥20% violations). Further, the mean difference of pre-transfusion Hemoglobin will be calculated, in order to assess adherence to the protocol.

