### 2.10 Screening, Baseline and Follow-up assessments

Potential participants will be identified by screening at HSCT transplant consultation and/or planning visits. Following written informed consent, demographic information will be collected and participants will be screened for eligibility at the screening visit (see Table 3 for study schedule and procedures at all study visits).

**Table 3 T3:** Schedule and Evaluation of Outcomes

		Study Entry	Scheduled Assessments (± 3 days as inpatient; ± 5 days as outpatient)					
			Day 0	Day 7	Day 14	Day 28	Day 60	Day 100
Demographics/Baseline characteristics	Trial Case Number	x						
	Date of Birth	x						
	Gender	x						
	Indication for HSCT	x						
	Stem cell Source	x						
	CD34 cell count	x						
	Donor Type (allos only)	x						
	HLA compatibility (allos only)	x						
	ABO blood type	x						
	ABO compatibility (allos only)	x						
	CMV compatibility (allos only)	x						
	Karnofsky Functional Scale	x						
	Conditioning regimen	x						
	HCT-CI	x						
	CBC	x	all available values					
Quality of Life Scales	EQ-5D and FACT-BMT†	x		x	x	x	x	x
Transfusion Assessments	Red Cells Transfusion Assessment		As needed					
	Platelets Transfusion Assessment		As needed					
	Plasma and Cryoprecipitate Transfusion Assessment		As needed					
Transplant Assessments	Bleeding Assessment				x	x		x
	Infection Assessment				x	x		x
	VOD Assessment^#^					x		
	Bearman Toxicity Assessment^					x		
	aGVHD*							x
	Admission to ICU		As needed					
	Hospital Admission		As needed					
	Mortality Assessment							x

NB Scheduled Assessments will be required even if the patient is discharged; the assumption is that no transplant toxicities have occurred if the patient is discharged

† Quality of Life Scales may be completed at home to be mailed or handed in

^# ^Presence/Absence within the 1st 21 days of HSCT (by Seattle Criteria) ^ Highest grade to be completed * Highest grade of aGVHD to be completed

HLA: Human Leukocyte Antigen; CMV: Cytomegalovirus; HCT-CI: Hematopoietic Cell Transplantation-Comorbidity Index; CBC: Complete Blood Count;

VOD: Veno-occlusive Disease; aGVHD: acute graft versus host disease; ICU: Intensive Care Unit

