### 2.15 Data Safety and Monitoring Board

The DSMB will be independent and composed of 3 members: an expert in HSCT, an expert in transfusion medicine, and an expert in clinical trials (chair). A DSMB charter will be provided to the DSMB. All serious adverse events will be reported to and reviewed by the DSMB. A DSMB meeting will be conducted once 25 patients have completed their treatment phase of the study. Subsequently, the DSMB will meet after every 25^th ^participant is randomized and reports to the co- PIs. Should safety issues arise that the DSMB feel compromises the trial and/or participant safety, then a meeting will be convened of all co-investigators to consider amending or stopping the trial. DSMB will receive three interim reports and can, at any time, recommend termination of the study in the event that it appears unsafe to continue. There is no stopping rules for this pilot study; the steering committee and DSMB will use their judgment in the event the trial has to be terminated early for safety concerns.

All interim reports (summarized by the study statistician) will include the following aggregated data: 1) Number of patients enrolled, 2) Proportion of patients at 28 days, 3) Proportion of patients at 100 days, 4) Number of autologous and allogeneic HSCTs, 5) Number of Red cell Transfusions, 6) Mean difference of pre-transfusion Hemoglobin (to assess adherence to the protocol), 7) Transfusion Reactions from Red cells, 8) Bleeding as per WHO scale, 9) Veno-occlusive Disease for recipients of Allogeneic HSCT, 10) Assessment of the Bearman Toxicity Score, 11) Acute GVHD for recipients of Allogeneic HSCT, 12) Number of hospitalizations (and length of each admission) from start of conditioning up until 100 days or death, whichever occurs first, 13) Number of ICU Admissions (and length of each admission) from start of conditioning up until 100 days or death, whichever occurs first, 14) Serious Adverse Events, 15) Grade 4 and 5 Infections and 16) Deaths. Further data will be provided to the DSMB when deemed necessary by the DSMB.

The board comprises of [name] (Chair), Program Director, Transfusion Medicine McMaster University, [name], HSCT Physician at Dalhousie University and [name], Transfusion Medicine Physician at Queens University.

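### Both adherence measures in section 2.7 are computed only on transfusions given, so liberal-arm transfusions that are withheld below trigger can go unregistered

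*Protocol article*

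**What the plan says.** Section 2.3 of the protocol article defines each strategy as a duty to transfuse 2 units whenever the day's hemoglobin is below the trigger (90 g/L liberal, 70 g/L restrictive), from Day 0 to Day 100. Each has a target range; the restrictive one reads "based on the day's CBC to target a Hb level of 70-90 g/L", and the liberal range is 90-110 g/L.

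Section 2.7 sets two adherence measures:

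- **Violation rate.** "Compliance will be assessed by the number of protocol violations for red cell transfusions", meaning red cells received off-trigger without a clinical rationale. The denominator is transfusion episodes: "We have arbitrarily defined compliance (based on total PRBC transfusion episodes) to the assigned red cell transfusion threshold as follows". The bands are "Excellent (≤5% violations), Acceptable (between 5% and 20% violations), Poor (≥20% violations").
- **Pre-transfusion hemoglobin.** "Further, the mean difference of pre-transfusion Hemoglobin will be calculated, in order to assess adherence to the protocol". Item 6 of the DSMB interim reports in section 2.15 repeats it: "Mean difference of pre-transfusion Hemoglobin (to assess adherence to the protocol").

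Neither place gives a value of the hemoglobin difference that counts as good. Table 3 in section 2.10 collects CBC results from Day 0 as "all available values", but the article names no comparison of these values between arms.

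**The concern.** Under section 2.3, not transfusing a liberal-arm patient at, say, 82 g/L departs from the strategy just as transfusing a restrictive-arm patient at that level does. The first leaves no transfusion episode. It adds nothing to the numerator or denominator of the violation rate and yields no pre-transfusion value.

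This kind of failure is foreseeable. In the survey reported in the Background, 14 of 15 centres transfuse below 80 g/L, one below 70 g/L, and none has clearly adopted a liberal strategy. The liberal arm asks staff to transfuse earlier than they are used to.

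The pilot is meant to inform a definitive trial. If under-delivery by omission is not registered, the pilot could report excellent compliance while the hemoglobin contrast that the definitive trial would rely on is small.

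**Working it through.** The plan states no figure for the hemoglobin contrast, so there is none to reproduce. The check has three steps.

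**1. What each measure can see**

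| Event | Violation rate | Pre-transfusion difference |
|---|---|---|
| Restrictive patient transfused above 70 g/L without clinical rationale | counted | falls |
| Liberal patient transfused late, well under 90 g/L | not counted if below-trigger transfusions are taken as compliant | falls |
| Liberal patient below 90 g/L, no transfusion that day | absent | absent |
| Patient never transfused | absent | absent |

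**2. Algebra, with no assumed hemoglobin course**

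Let L and R be the mean hemoglobin over all patients and days in the liberal and restrictive arms under full adherence, and U the mean with no transfusion at all. Suppose a fraction f of liberal patients, otherwise comparable to the rest, is never transfused.

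- Pre-transfusion difference: unchanged in expectation, because those patients supply no values. If transfusions follow the triggers it stays near 90 − 70 = 20 g/L.
- Violation rate within the liberal arm: unchanged in expectation.
- All-patient difference: (1 − f)(L − R) + f(U − R). Since U is no higher than R, this is at most (1 − f)(L − R).

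With f = 0.5, the true contrast is at most half its full-adherence value, and neither adherence measure moves.

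**3. Illustrations (hemoglobin courses are assumptions; the documents give none)**

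*Course A:* Day 0 hemoglobin 100 ± 10 g/L, falling about 2 g/L per day to about Day 14, then rising about 0.6 g/L per day; 2 units add 18 g/L.

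| Liberal arm | Pre-transfusion difference (g/L) | All-patient difference, Days 0-28 (g/L) |
|---|---|---|
| Full adherence | 19.6 | 14.5 |
| Half never transfused | 19.5 | 4.5 |
| Half managed at trigger 70 | 14.8 | 14.5 / 2 = 7.25 (algebra) |
| All managed at trigger 80 | 9.9 | 6.5 |

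The second row agrees with step 2: the bound is 0.5 × 14.5 = 7.25, and 4.5 implies U − R = (4.5 − 7.25) / 0.5 = −5.5 g/L. Under full adherence the all-patient difference is only about 7 g/L over Days 61-100. The Background says of one allogeneic cohort, after Day 60, that "the frequency of red cell transfusion decreased significantly thereafter", so few pre-transfusion values may describe that period.

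*Course B:* three depths of marrow suppression. Day 0 hemoglobin is about 105, 110 or 115 g/L, falling 2.5, 1.8 or 1.2 g/L per day for about 14, 10 or 9 days; each unit adds 10 g/L. All-patient differences are over Days 0-100.

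| Scenario | Pre-transfusion difference (g/L) | All-patient difference (g/L) | Counted violations |
|---|---|---|---|
| Marked suppression, full adherence | 19.8 | 10.4 | 0% |
| Mild, full adherence | 19.4 | 6.0 | 0% |
| Very mild, full adherence | 20.3 | 2.0 | 0% |
| Marked, 50% of liberal below-trigger days skipped | 17.8 | 9.3 | 0% |
| Marked, 90% skipped | 7.3 | 3.5 | 0% |
| Marked, some restrictive transfusions at 70-90 g/L | 15.4, 9.4, 4.2 | 8.5, 4.4, 1.5 | 28%, 67%, 92% (restrictive arm) |

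The violation rate reads 0% however many liberal transfusions are skipped. The pre-transfusion difference reacts when transfusion is late or above trigger. It does not react when patients are left out entirely, and it does not track the all-patient contrast when few need blood.

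**The case against.** The strongest reply has four parts.

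- **Role.** The article offers the pre-transfusion difference for adherence, as an addition to the banded violation rate. A reader might infer that it is the trial's measure of arm separation, or that the DSMB would take 20 g/L as proof of contrast. The text says neither and sets no such value.
- **Responsiveness.** A reader might also infer that the two triggers fix the difference near 20 g/L. They do so only when the transfusions given follow the triggers. The coordinating centre's audit found 20% of episodes above its trigger, and above-trigger transfusion in the restrictive arm does lower the measure. So do lower triggers in the liberal arm.
- **Extremity.** Never transfusing half the liberal arm means less blood than the restrictive rule gives, which sits badly with the surveyed practice of transfusing below 80 or 70 g/L.
- **Other checks.** Section 2.16 compares red cell units between arms by intention to treat, and DSMB item 5 gives the number of red cell transfusions. In the half-untransfused case under course A, liberal units fall from about 3.2 to 1.6 per patient against 1.0 restrictive, so the gap shrinks from 2.2 to 0.6 units.

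All four stand as limits on the point. None supplies a measure that counts a withheld transfusion. The violation rate shares the blind spot, and unit counts show neither the hemoglobin achieved nor the below-trigger days left untreated. The full protocol or analysis plan may add a hemoglobin summary by arm. The point here concerns the two measures that the article does fix.

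**Conclusion.** The point holds in this limited form: neither adherence measure in section 2.7 registers omitted transfusions, so compliance can read as excellent while the liberal strategy is under-delivered. That much follows from the definitions, given that below-trigger transfusions count as compliant.

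The size is not determined by the documents. Under the assumed courses, a pre-transfusion difference of about 19-20 g/L went with an all-patient difference anywhere from 14.5 g/L (Days 0-28, full adherence) to 4.5 g/L (Days 0-28, half the liberal arm untransfused) or 2.0 g/L (Days 0-100, full adherence, very mild suppression). The last shows a small contrast with no adherence failure, so it bears on planning the definitive trial and not on compliance. The pre-transfusion difference is an incomplete measure, and the documents do not support calling it uninformative.

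**What to change.** In section 2.7 and item 6 of the DSMB report list, add two measures from the CBC values that Table 3 already collects:

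1. The between-arm difference in each patient's mean hemoglobin over all available values, in all randomised patients, for Days 0-28, 29-60 and 61-100 and by transplant type.
2. The share of below-trigger CBC days followed by a transfusion, by arm.

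Keep the violation rate and the pre-transfusion difference, labelled as descriptions of the transfusions given.

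The cost is a little more analysis and no new data. The reported hemoglobin difference will probably be smaller than the pre-transfusion figure.
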